### Secondary outcomes

**
*1. e-ASPECTS processing success and factors influencing accuracy.*
** To present the most complete picture available, we will use the entire RITeS sample for these analyses (i.e. not just the representative sample) but we will also include a sensitivity analysis of the representative sample.

We will report the proportion of scans successfully and unsuccessfully processed by e-ASPECTS and collate reasons cited by e-ASPECTS for any processing failures. We will use summary statistics to describe and compare the subgroups of scans that were successfully versus unsuccessfully processed. This will include patient and radiological factors (see Table 4).

To determine the influence of patient and radiological factors on the accuracy of ASPECTS results produced by e-ASPECTS software, we will perform multivariable ordinal logistic regression using the variables pre-specified in Table 5. The dependent variable will be the absolute difference in ASPECTS between e-ASPECTS and expert human readers (i.e. scalar, 0-10).

For any variables found to be significantly associated with poorer e-ASPECTS results on regression testing (i.e. independently associated with greater difference between e-ASPECTS and expert human reader scores), we will also calculate and compare diagnostic accuracy figures (as above) for each of the subgroup arms (for these analyses only, continuous data will be dichotomised as per Table 5).

Finally, to account for (the as yet unknown) covariates that alter e-ASPECTS diagnostic accuracy figures, we will derive covariate-adjusted ROC curves (AROC)^50^.

**
*2. Identification of CTA obstruction and collateral scoring by e-CTA versus expert human readers.*
** There are two components to the e-CTA output: 1. Where ICA-MCA occlusion is identified, the location is categorised either proximal (ICA/proximal MCA) or distal (distal MCA). Other arteries are not assessed.2. MCA collateral scoring (modified Tan *et. al*. 2009)^51^ is given for all cases on the scale 0 = no collaterals (<10% of affected MCA territory compared to contralateral side), 1 = poor (10–50%), 2 = good (50–90%), 3 = excellent (>90%) collaterals (i.e. includes normal scans).

The expert human rated CTAs available to RITeS include similar scoring methods for comparison with e-CTA outputs, but also additional measures such as degree of arterial patency (i.e. from fully patent through increasingly obstructed to occluded)^22^.

We will test three components: 1. The proportion of scans where e-CTA and expert humans agree or disagree in the assessment of proximal versus distal ICA-MCA axis occlusion, see Table 6. We will use K-alpha statistics to compare agreement for ICA-MCA axis occlusion detected by e-CTA and expert human readers.2. Diagnostic accuracy of e-CTA for detecting abnormal versus normal intracranial CTA using the methods described above. Abnormal will include both arterial obstruction (partially blocked) and arterial occlusion (completely blocked) for 11 named intracranial arterial segments, i.e. not just ICA or MCA; we will also assess the anterior and posterior cerebral arteries (ACA and PCA, respectively), the vertebral and basilar arteries (five left, five right, one central).3. Agreement on collateral score. Most of the expert collateral scoring available in RiTeS used the Miteff method (three-point scalar = good, moderate, poor)^23^, rather than the modified Tan method (4-point scalar = excellent, good, poor, none) but as ordinal scores, these are comparable. There are three ways to compare the scores (see Table 7). We will test all variations for agreement. We will use K-alpha statistics to check the extent of agreement between e-CTA and human-rated results for the scalar collateral scoring.

**
*3. Repeatability of e-ASPECTS and e-CTA results.*
** We will select a small subgroup of RITeS scans for repeat e-ASPECTS and e-CTA testing. These subgroup sizes were arbitrarily chosen within available time and scan processing resource limitations.

We will include separate assessments of ASPECTS (n=100), haemorrhage detection (n=20) and CTA scoring (n=20). We will select scans for repeat testing, blind to all previous results (from e-ASPECTS, e-CTA or expert human readers) except knowledge of previous successful processing by e-ASPECTS or e-CTA. To ensure this subsample remains largely representative of the available stroke trial mix, we will use cluster random sampling, as follows. Each stroke trial represents a cluster. Random samples will be drawn from each cluster in numbers to match individual stroke trial proportions in the entire representative sample until the total numbers required are reached for each of the separate assessment groups, total n=140.

To limit the possibility of previously calculated results being presented again (rather than freshly derived from the ‘new’ scan), selected scans will have all unique identifiers replaced prior to repeat e-ASPECTS/e-CTA processing. This includes original trial IDs and any other DICOM information that uniquely identifies individual scans (e.g. accession number, series/scan unique identifiers).

We will compare original and repeat results for agreement, as per Table 8. We will use Mann-Whitney U tests to compare scalar and non-parametric continuous group data, and K-alpha to compare paired scan results.

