### Secondary outcomes

1. Proportion of scans successfully versus unsuccessfully processed by e-ASPECTS (i.e. where ASPECTS results are provided or not provided), factors associated with e-ASPECTS processing success and result accuracy.2. Proportion of ICA-MCA occlusion versus normal ICA-MCA axis correctly identified by e-CTA, accuracy of e-CTA for detecting any intracranial obstruction, difference in CTA collateral scores provided by e-CTA versus expert human readers.3. Repeatability of e-ASPECTS and e-CTA results on a subset of scans presented twice.

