## Statistical analysis

### Analysis principles and general considerations

Primary and where appropriate, secondary outcome testing will be conducted on an ‘intention-to-analyse’ basis irrespective of whether scan processing was successful or not◦ Processing will be considered successful when an ASPECTS (0-10) or CTA result (occlusion/no-occlusion or scalar collateral score) is provided, or when arterial hyperattenuation or haemorrhage is detected.◦ We will record all software failures whether these occur at the scan upload, scan processing, or results output stage.We will use mean (standard deviation, SD) or median (inter-quartile range, IQR) to represent the distribution of parametric and non-parametric data, respectively. We will use n (%) for categorical data.Where possible, we will use diagnostic accuracy statistics as the principal method in RITeS for comparing software and expert human results. With expert human results as the reference standard, we will calculate true/false positive/negative cases (TP, FP, TN, FN, respectively) and derive sensitivity (TP/TP+FN), specificity (TN/TN+FP), positive predictive (TP/TP+FP), negative predictive (TN/TN+FN), and accuracy (TP+TN/TP+TN+FP+FN) percentages as standard. We will calculate 95% confidence intervals for each using the Wilson score method^37^. ◦ For all diagnostic accuracy testing we will include random-effects meta-analysis modelling of individual patient data (i.e. a one-step meta-analysis) to provide overall estimates of sensitivity and specificity, to assess variation within and between the 10 RITeS studies, and to account for clustering of individual study results^38^,^39^.◦ For each of the 10 RITeS studies, we will use the PROBAST method for assessing risk of bias in diagnostic modelling^40^. For all comparisons of software and expert human results, we will review side of affected brain data to ensure ASPECTS and CTA results are correctly matched for each cerebral hemisphere, i.e. matched results require same score and side. We will separately test whether knowledge of affected side impacts the accuracy of e-ASPECTS results, see secondary outcomes below.Bland-Altman plots^41^ will be used to visually compare software and expert human results, comparing mean score differences to assess the magnitude, direction and distribution of error and will use ± 1.96 SD to determine the range of agreement^42^. For software and expert human results to be considered equivalent, we will set maximum clinically acceptable limits of agreement for individual scores, specified in the relevant sections below.Krippendorff’s Alpha^43^ (K-alpha) will be used to assess reader (human-human and human-software, as necessary) agreement. K-alpha is generally more robust than kappa in this context since it can handle categorical and ordinal data, works where there is missing data, adjusts for small sample sizes, and includes multiple observers simultaneously^43^,^44^. K-alpha results are interpreted similarly to kappa with scores ranging from -1 (perfect disagreement) to +1 (perfect agreement). We will therefore also use the Landis and Koch method for interpreting K-alpha results (as commonly used for kappa): 0.00–0.20=slight agreement, 0.21–0.40=fair agreement, 0.41–0.60=moderate agreement, 0.61–0.80=substantial agreement and 0.81–1.00=almost perfect agreement^45^.Other specific statistical tests are listed in the following sections.For multivariable testing, we will check for multicollinearity between included variables by identifying variance inflation factors (VIF) >5. Where multicollinearity is detected, we will run separate (but otherwise equivalent) multivariable regression models for each of the internally correlated variables.We will not impute but will report missing data (proportions of data missing for each variable and observations not included in analyses).We will use SPSS, IBM Corporation (Armonk, USA) and/or R (https://www.r-project.org/) statistical software for all analyses. We will preferentially report 95% confidence intervals, but where appropriate, we will report p-values.

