
### Primary outcomes

For these evaluations of e-ASPECTS, we will use a representative RITeS sample of NECT.

In two analyses, we will compare e-ASPECTS results to those provided by expert human readers for the assessment of non-enhanced brain CT acquired at baseline among patients presenting acutely with symptoms of stroke.

**
*Representative sampling for e-ASPECTS testing of primary outcomes.*
** Where clinical or demographic features are different to the comparator SSNAP/STTC/HERMES datasets (i.e. RITeS values should be within the range provided by the other datasets), we will use stratified random sampling to remove select cases (which are over-representing these features) to reduce these differences while maintaining the maximum sample size from the data available to RITeS. For example, if RITeS has 42% female patients and a median NIHSS of 19, we would identify all male patients with a high NIHSS and randomly remove subsets of these until the sex ratio and NIHSS are within the desired ranges. We will not select cases on the basis of the radiological features in Table 3.

To assess the impact of factors beyond our control which might affect the representativeness of our sample, we will perform sensitivity analyses of our primary outcomes for the following randomly selected subgroups: 1. With balanced representation from all RITeS trials, i.e. we will exclude surplus cases for trials which are relatively over-represented (more than double the median trial contribution).2. Where non-stroke mimics represent 26% of the total sample.

**
*1. Difference in ASPECT scores of e-ASPECTS and expert human readers.*
** We will compare e-ASPECTS and expert human results using overlapping histograms and Mann-Whitney U testing to assess the distribution of results, and Wilcoxon signed rank testing and Bland-Altman plots to assess pairwise agreement for each case. For results to be considered equivalent on Bland-Altman testing, we expect the range of agreement to be within ± 2 ASPECTS points. This is an arbitrarily derived but clinically meaningful difference that might lead to alterations in treatment for individual patients based on the thresholds presented below. We will also use K-alpha statistics to assess software-human reader agreement for these scalar data.

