**Table 3. T3:** Planned assessment of radiological characteristics of the entire RITeS dataset.

Radiological Finding		N (%) or Median (IQR)
Ischaemic brain changes	None	
	Subtle (e.g. loss of grey-white margins)	
	Obvious (e.g. hypoattenuation relative to normal white matter +/- swelling)	
Ischaemic location	MCA territory	
	Other cerebral	
	Brainstem or cerebellum	
	Cortical	
	Subcortical	
Hyperattenuating arteries	List location	
Haemorrhage location	Deep	
	Lobar	
	Intraventricular	
	Extra-axial	
Structural stroke mimic	List type (e.g. tumour, inflammation, collection)	
Pre-stroke brain changes	Atrophy	
	Leukoaraiosis	
	Old Stroke lesions	
CT slice thickness	Thin (≤ 1 mm)	
	Medium (> 1 mm ≤ 5 mm)	
	Thick (> 5 mm)	

**Table 4. T4:** Planned univariable comparison of scans successfully versus unsuccessfully processed by e-ASPECTS.

Variable	Successfully Processed	Not Successfully Processed	Absolute differences, 95% CI and p-value
Patient age (median, IQR)			
Patient sex (n, %)			
Minutes from stroke onset to scan (median, IQR)			
NIHSS (median, IQR)			
Stroke aetiology (n, %): • Ischaemia MCA territory • Ischaemia elsewhere • Haemorrhage • Mimic			
Presence of pre-stroke brain changes (n, %): • Atrophy • Leukoaraiosis • Old stroke lesions			
CT slice thickness (n, %): • ≤ 1 mm • > 1 mm ≤ 5 mm • > 5 mm			
Image quality (n, %): • Good quality • Movement artefacts • Streak artefacts • Patient malposition			

Note: IQR = Inter-quartile range. MCA = middle cerebral artery. NIHSS = National Institutes of Health Stroke Scale.

**Table 5. T5:** Variables for multivariable analysis and subgroups for diagnostic accuracy testing.

Clinical Characteristics		Imaging Findings		Imaging Technique	
Age	≤60 years	ASPECTS	<6	CT slice thickness	≤1 mm
	>60 years		≥6		> 1 mm
NIHSS	0–6	Infarct Location	MCA territory	Poor patient positioning	Yes No
	7–12		Elsewhere		
	>12	Atrophy, Leukoaraiosis, Old stroke lesion	Yes No		
Time from stroke onset to scan	<3 hours				
	3+ hours			Imaging artefact (movement or streak)	
Knowledge of affected side	Yes No				

**Table 6. T6:** Comparison of ICA-MCA axis occlusion identified by e-CTA and expert-human groups.

Human Readers e-CTA	Proximal Occlusion	Distal Occlusion	TOTAL
Proximal Occlusion			
Distal Occlusion			

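### Factors associated with e-ASPECTS processing success are tested only by pooled univariable comparisons, with no adjustment between factors and no account of source trial

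*SAP article*

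**What the plan says.** In the Methods of the SAP article, item 1 of the secondary outcomes covers "factors associated with e-ASPECTS processing success and result accuracy". The abstract gives the matching aim: to test when and why the software is more or less accurate, or does or does not return a result.

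The Statistical analysis section treats the two halves differently.

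- **Processing success.** "We will use summary statistics to describe and compare the subgroups of scans that were successfully versus unsuccessfully processed". Table 4 is titled "Planned univariable comparison of scans successfully versus unsuccessfully processed by e-ASPECTS" and its last column is "Absolute differences, 95% CI and p-value". Its rows are age, sex, onset-to-scan time, NIHSS, aetiology, pre-stroke brain changes, slice thickness and image quality. Source trial is not among them. The sample is pooled: "we will use the entire RITeS sample for these analyses", with a sensitivity analysis in the representative sample.
- **Accuracy.** This gets a multivariable ordinal logistic regression on the Table 5 variables: "The dependent variable will be the absolute difference in ASPECTS between e-ASPECTS and expert human readers".

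Two provisions elsewhere deal with source trial. Under the analysis principles: "For all diagnostic accuracy testing we will include random-effects meta-analysis modelling of individual patient data". Under the primary outcomes, one of the subgroups is balanced by trial: "we will perform sensitivity analyses of our primary outcomes for the following randomly selected subgroups".

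**The concern.** A question about which factors go with software failure is answered by a set of separate crude tests on scans pooled from 10 studies. Two problems follow.

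1. A factor that is commoner in a trial with a high failure rate will look associated with failure even if it has no effect within any trial.
2. Factors that tend to occur together, such as age, atrophy, leukoaraiosis and old stroke lesions, will tend to appear together. Separate tests cannot say which of them matters, even within one trial.

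With about 6,600 scans, a modest imbalance can produce a confidence interval that excludes no effect. At stake is the guidance that readers take from this secondary outcome about the patients or scans on which the software is likely to fail. No primary result is affected.

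**Working it through.** **1. The plan's own figure for processing failure.** The sample size section allows for up to 31% failure and inflates 500 scans to 725. Check: 500 / (1 − 0.31) = 500 / 0.69 = 724.6, rounded up to 725. This reproduces and is not in dispute.

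**2. Does any other provision reach this outcome?**

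| Provision | Scope as written | Covers processing success? |
|---|---|---|
| Ordinal regression, Table 5 | Score difference, software against experts | No: a scan without an ASPECTS has no difference and drops out |
| Random-effects modelling of individual patient data | Diagnostic accuracy testing | No |
| Trial-balanced sensitivity analysis | Primary outcomes | No |
| Representative-sample sensitivity analysis | This outcome | Yes, but cases are removed on clinical and demographic features, not by trial |
| Failure reasons cited by the software | This outcome | Yes, but this does not separate factors from each other or from trial |

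**3. How the pool is made up (Table 1).** The rows sum to 104 + 98 + 3035 + 947 + 65 + 113 + 271 + 537 + 1149 + 293 = 6,612.
- IST-3: 3,035 / 6,612 = 45.9%.
- LINCHPIN and RESTART, the two haemorrhage studies: (947 + 537) / 6,612 = 1,484 / 6,612 = 22.4%. The haemorrhage row of Table 4 is therefore largely a trial label.

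**4. Illustration with slice thickness.** From Table 1: IST-3 n = 3,035, other trials n = 3,577. Assumed, because the SAP gives no trial-level values: failure rates, share of thick slices, and no effect of slice thickness within IST-3 or within the rest.

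With a, b = failed and successful thick-slice scans and c, d = the same for other scans, crude OR = ad / bc and SE(log OR) = √(1/a + 1/b + 1/c + 1/d). For failure of 31% and 25% and thick slices in 80% and 30%:
- a = 3,035 × 0.8 × 0.31 + 3,577 × 0.3 × 0.25 = 752.7 + 268.3 = 1,021.0
- b = 1,675.3 + 804.8 = 2,480.1
- c = 188.2 + 626.0 = 814.1
- d = 418.8 + 1,877.9 = 2,296.8
- OR = (1,021.0 × 2,296.8) / (2,480.1 × 814.1) = 1.16; SE = 0.055; 95% CI 1.04 to 1.29.

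The Mantel-Haenszel OR, Σ(AᵢDᵢ/nᵢ) / Σ(BᵢCᵢ/nᵢ), is 1.00, because AᵢDᵢ = BᵢCᵢ in each stratum.

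| Failure, IST-3 / rest | Thick slices, IST-3 / rest | Crude OR (95% CI) | Stratified OR |
|---|---|---|---|
| 31% / 25% | 80% / 30% | 1.16 (1.04–1.29) | 1.00 |
| 31% / 20% | 80% / 30% | 1.34 (1.20–1.50) | 1.00 |
| 31% / 10% | 80% / 30% | 1.98 (1.75–2.25) | 1.00 |
| 31% / 10% | 60% / 40% | 1.30 (1.15–1.47) | 1.00 |
| 31% / 31% | 80% / 30% | 1.00 (0.90–1.11) | 1.00 |
| 31% / 10% | 50% / 50% | 1.00 (0.89–1.13) | 1.00 |

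The last two rows show that both failure rate and factor mix must differ between trials before any bias arises.

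**5. The same with age.** Assumed: no age effect within IST-3 or within the rest, SD 13, mean ages and failure rates as shown. z = difference / (13 × √(1/n_fail + 1/n_ok)).
- 77 years and 31% failure in IST-3 against 70 years and 15% elsewhere: n_fail = 940.9 + 536.6 = 1,477.4, n_ok = 5,134.6; mean ages 74.46 and 72.86; difference 1.6 years, z = 4.2.
- 77 years and 35% against 68 years and 10%: difference 3.3 years, z = 8.5.

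**6. What a single adjusted model would lose.** The SAP gives NIHSS for ischaemic and GCS for haemorrhagic stroke, and rules out imputation. A complete-case model with every Table 4 variable would therefore drop both haemorrhage studies, 1,484 of 6,612 (22%). Table 1 lists no pre-stroke change or image quality ratings for ATTEST (104), POSH (113) or SITS Open (293). If that listing is complete, the loss is 1,484 + 510 = 1,994 (30%).

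**The case against.** A reader might infer that trial differences will be reported as causes of software failure. The documents do not support that. They give no age, severity, scanner, slice thickness or failure rate by trial; the 31% is one upper figure taken from a cited source. The plan speaks of association, labels Table 4 as univariable, and keeps its language of influence and independent association for the accuracy model. No rule draws a causal conclusion from Table 4. All of this stands.

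The plan also has other information on why scans fail: the reasons given by the software, a record of the stage at which failure occurred, and a STARD-type flow chart. Table 4 shows absolute differences and intervals, so in the first age example a reader would see a gap of only 1.6 years and not just a small p-value. This also stands, and it limits the harm.

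It does not remove the point. Factors associated with success are a named secondary outcome, each will carry an interval and a p-value, and the plan allows for clustering by trial elsewhere but not here. The objection that one model with all Table 4 variables would discard whole studies is correct, and it shapes the fix.

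**Conclusion.** The point holds as a weakness in the analysis of part of one secondary outcome. The comparison is univariable, pooled and without a trial term, and nothing else in the plan fills the gap. Trial differences can therefore appear as patient or imaging associations, and correlated factors cannot be told apart.

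Whether the first of these will happen, and how strongly, cannot be known from the SAP. On the assumed inputs the spurious odds ratio runs from 1.00, when failure rate or factor mix is equal across trials, to about 2. The trial shares of 46% and 22% come from Table 1; the trial-level failure rates, ages and slice mixes are assumptions. This is a desirable improvement and does not threaten the primary results.

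**What to change.** - Keep Table 4 and state that it is an unadjusted descriptive display.
- Report the failure rate for each trial.
- Add a logistic model for success against failure with a random intercept for trial (or trial strata), on a core set of variables available in all trials, for example age, sex, onset-to-scan time and slice thickness.
- Fit a second model that adds NIHSS and the pre-stroke change and image quality ratings, restricted to the trials that recorded them.
- Base statements about factors on these two models. State that haemorrhage aetiology is largely tied to trial and so will be poorly separated from it.

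The cost is one or two extra models. No new data should be needed, since trial identifiers are kept at anonymisation. At the 31% upper figure the full pool would hold about 0.31 × 6,612 = 2,050 failures. The second model would have 6,612 − 1,994 = 4,618 scans if Table 1 lists all ratings, and about 0.31 × 4,618 = 1,430 failures if the same rate applied there. The downside is that reduced sample and its silence on the haemorrhage studies.

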## Abstract

**Background:** Artificial intelligence-based software may automatically detect ischaemic stroke lesions and provide an Alberta Stroke Program Early CT score (ASPECTS) on CT, and identify arterial occlusion and provide a collateral score on CTA. Large-scale independent testing will inform clinical use, but is lacking. We aim to test e-ASPECTS and e-CTA (Brainomix, Oxford UK) using CT scans obtained from a range of clinical studies.

**Methods:** Using prospectively collected baseline CT and CTA scans from 10 national/international clinical stroke trials or registries (total >6600 patients), we will select a large clinically representative sample for testing e-ASPECTS and e-CTA compared to previously acquired independent expert human interpretation (reference standard). Our primary aims are to test agreement between software-derived and masked human expert ASPECTS, and the diagnostic accuracy of e-ASPECTS for identifying all causes of stroke symptoms using follow-up imaging and final clinical opinion as diagnostic ground truth. Our secondary aims are to test when and why e-ASPECTS is more or less accurate, or succeeds/fails to produce results, agreement between e-CTA and human expert CTA interpretation, and repeatability of e-ASPECTS/e-CTA results. All testing will be conducted on an intention-to-analyse basis. We will assess agreement between software and expert-human ratings and test the diagnostic accuracy of software.

**Conclusions:** RITeS will provide comprehensive, robust and representative testing of e-ASPECTS and e-CTA against the current gold-standard, expert-human interpretation.

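### Screening factors on the unsigned ASPECTS error, and calculating subgroup accuracy only after a significant result, can pass over a factor that trades missed lesions for false alarms

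*SAP article*

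**What the plan says.** The Abstract sets the aim: "Our secondary aims are to test when and why e-ASPECTS is more or less accurate". The first secondary outcome in the Statistical analysis section carries it out in two steps.

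- **Screen.** The plan states "we will perform multivariable ordinal logistic regression using the variables pre-specified in Table 5". The outcome is defined thus: "The dependent variable will be the absolute difference in ASPECTS between e-ASPECTS and expert human readers", on a scale given as 0-10. Tables 4 and 9 use the term absolute difference for an ordinary difference between groups. Here the 0-10 range rules out negative values, so the sign of the error is dropped.
- **Follow-up.** The next step opens "For any variables found to be significantly associated with poorer e-ASPECTS results on regression testing" and explains poorer as "independently associated with greater difference between e-ASPECTS and expert human reader scores". For those variables only, "we will also calculate and compare diagnostic accuracy figures (as above) for each of the subgroup arms".

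Table 5 is captioned "Variables for multivariable analysis and subgroups for diagnostic accuracy testing", so the subgroups are fixed in advance. No other section provides their accuracy figures independently of the screen.

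**The concern.** The two steps measure different things. The screen asks whether the size of the scoring error differs between levels of a factor. The follow-up reports sensitivity and specificity, which depend on which scans carry the errors. Under-scoring a normal scan by two points and over-scoring a lesion scan by two points count the same in the screen. In the follow-up, the first is a false alarm and the second a miss. A factor that exchanges one for the other can leave the screening outcome almost unchanged.

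False alarms and missed ischaemia have different clinical meaning, and this analysis is the one meant to show where the software does worse. The general considerations also promise a test of whether knowing the affected side alters accuracy. In the secondary outcomes that question appears only as a Table 5 variable, so it goes through the same screen. Conditioning on significance also selects which subgroup results appear.

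**Working it through.** The plan gives no figure for this point. It does not state the share of scans with a lesion, the software's error rates or the significance level of the screen. Those below are assumptions, with 0.05 as the level.

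**1. Exact example.** Take 1000 scans at each level of a factor: 500 with expert score 10 and 500 with expert score 8. Every error is 2 points, and the cut-point is the plan's 10 versus 0-9.

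| | Factor absent | Factor present |
|---|---|---|
| False alarms | 150 | 50 |
| Misses | 50 | 150 |
| Sensitivity | 450/500 = 90% | 350/500 = 70% |
| Specificity | 350/500 = 70% | 450/500 = 90% |
| Unsigned difference 2 / 0 | 200 / 800 | 200 / 800 |
| Mean signed difference | (-300 + 100)/1000 = -0.2 | (-100 + 300)/1000 = +0.2 |

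The screening outcome has the same distribution at both levels, so no sample size would reveal this factor.

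**2. Sample size.** The Table 1 trials labelled ischaemic give 104 + 98 + 3035 + 65 + 113 + 271 + 1149 + 293 = 5128 patients. With the plan's upper figure of 31% processing failures, 5128 × 0.69 = about 3540. I use n = 3500 with the factor in 40%: 1400 scans with it and 2100 without.

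**3. A 10-point trade-off.** The factor moves sensitivity from 75% to 85% and specificity from 85% to 75%, with errors of equal size. For lesion share L, the error rate is 0.25L + 0.15(1 - L) without the factor and 0.15L + 0.25(1 - L) with it.

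- L = 40%: 19% versus 21%. SE = √(0.19×0.81/2100 + 0.21×0.79/1400) = 0.0139, z = 0.02/0.0139 = 1.44, power about 30%.
- L = 45%: 19.5% versus 20.5%, z about 0.72, power about 11%.
- L = 50%: 20% at both levels, so rejection is at the nominal level.
- Direct test of sensitivity at L = 40% (840 and 560 lesion scans): SE = √(0.75×0.25/840 + 0.85×0.15/560) = 0.0212, z = 4.7, power above 99%.

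Simulation with 1000 replicates agrees. The unsigned test rejects in 31%, 10%, 4%, 11% and 28% of samples at lesion shares of 40%, 45%, 50%, 55% and 60%, against at least 99% directly. An ordinal logistic model with graded errors at a 50% share rejects in 4.5%.

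**4. Where the loss fades.** At L = 30% the same trade-off gives 18% versus 22%, z = 0.04/0.0139 = 2.9, power about 82%. A 20-point trade-off (70% versus 90%) is detected in 30%, 6% and 30% of samples at lesion shares of 45%, 50% and 55%, but in about 83% at 40% or 60%.

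**5. The planned type of model.** A second simulation fitted an ordinal logistic model adjusted for expert ASPECTS below 6, with graded errors, 50% abnormal scans and the factor in half of them. Sensitivity falls from 80% to 60%, and specificity starts at 70%. Each cell has 50 to 150 runs, so the percentages are approximate.

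| Specificity moves to | n = 500 | n = 2000 | n = 5000 |
|---|---|---|---|
| 70% (no offset) | 44% | 95% | 100% |
| 75% | 19% | 62% | 96% |
| 85% | 3% | 6% | 2% |

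Entries are the share of runs in which the screen is significant. Adjusting for the expert score does not help, because the effect is an interaction with that score and none is planned.

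**6. Signed difference.** When specificity moves from 70% to 90% in the same simulation, a rank test on the signed difference detects the factor in 97-99% of runs at n = 500 and in 100% at n = 2000 and 5000, for 40-60% abnormal scans.

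**The case against.** Absolute error is a coherent outcome for how close a 0-10 score comes to the expert's, and the primary score comparison also uses a symmetric tolerance of ± 2 points. A reader might infer that the regression measures the wrong thing because accuracy in this plan means sensitivity and specificity. The document does not support that. Its general considerations also define predictive values and overall accuracy, and in the exact example overall accuracy is 80% at both levels, in line with a null regression.

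A reader might also infer that the plan treats a non-significant factor as having no effect on accuracy. It does not say so. It states for which variables further figures follow and draws no conclusion about the rest.

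The harm also needs near-cancellation at the actual case mix, which the documents do not give. Gating limits a large family of comparisons, and the sample size section warns of limited power for subgroups at the minimum sample. The n = 500 results matter little here, since this analysis uses the entire RITeS sample.

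There are partial safeguards. Bland-Altman plots examine direction, sensitivity and specificity are reported overall at three cut-points, and covariate-adjusted ROC curves are planned. None is promised for each Table 5 factor. A sensitivity-specificity trade-off can also be a move along one ROC curve, which an adjusted curve need not reveal.

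These objections narrow the point. They do not remove it, because the unsigned outcome and the gate together can still hide offsetting errors.

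**Conclusion.** The point holds in limited form. The unsigned model is incomplete, not invalid. A factor whose effects on misses and false alarms nearly offset can fail the screen, and the plan then makes no provision for its subgroup sensitivity and specificity.

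Under the assumptions above (about 3500 scans, factor in 40%, a 10-point trade-off, equal-sized errors), the screen finds it in about 4-31% of samples at lesion shares of 40-60%. Direct comparison finds it in at least 99%. Outside that range, or with weak offsetting in a large sample, the screen usually works, and a factor that only lowers sensitivity is usually caught. A claim that the screen generally misses factors behind missed ischaemia would go too far.

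This is a secondary analysis and neither primary outcome depends on it. The change is a worthwhile, inexpensive improvement.

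**What to change.** 1. Keep the unsigned ordinal model, described as a summary of error size.
2. Add the same multivariable model with the signed difference (e-ASPECTS minus expert) as outcome. Alternatively, fit logistic models for a software-positive result among expert-positive and, separately, among expert-negative scans at the pre-specified cut-points. The signed model should not replace the unsigned one, since it would miss a factor that enlarges errors equally in both directions.
3. Report sensitivity and specificity with 95% confidence intervals for every Table 5 subgroup, whatever the regression p-value, labelled exploratory.

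No new data are needed, and the subgroups and cut-points are already fixed. The cost is revised wording, a longer supplementary table and more exploratory comparisons to be read with caution.
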